## Discussion

### Potential and implementation of the findings

Reports of increases in PPH incidence in high-resource countries [3, 58, 59] underline the need for prophylaxis that goes beyond the current recommendation for the administration of a uterotonic at the start of the third stage of labor. PPH prevention might be enhanced by a treatment that acts on the coagulation process. Tranexamic acid, as an inexpensive agent that is simple to administer, could easily be added to the routine management of cesarean deliveries worldwide. It is thus a promising candidate for prevention. Nonetheless, the evidence now available does not justify its widespread use in this situation. This large, multicenter, randomized placebo-controlled trial aims to determine with adequate power if the benefits of the routine prophylactic use of tranexamic acid after cesarean delivery significantly outweigh its risks for the safe prevention of PPH.

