**Discussion:**

As an, inexpensive, easy to administer drug that can be add to the routine management of cesarean births in delivery rooms, tranexamic acid is a promising candidate for preventing PPH after these births. This large, adequately powered, multicenter randomized placebo-controlled trial seeks to determine if the benefits of the routine prophylactic use of tranexamic acid after cesarean delivery significantly outweigh its risks.

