##### For prevention of postpartum hemorrhage

We searched Medline through January 1, 2019, and found 20 RCTs aimed at evaluating the preventive impact on PPH of tranexamic acid administered after delivery in addition to prophylactic uterotonics [19–38]. Only four enrolled women with vaginal deliveries [19–22], the sixteen others including women with cesarean delivery [23–38]. Except for the French Tranexamic Acid for Preventing Postpartum Hemorrhage Following a Vaginal Delivery (TRAAP) trial, which we coordinated and on which this protocol is modeled [22, 39], these RCTs took place in countries with low or middle resources (China, India, Iran, Turkey, Pakistan, and Egypt), had major methodological flaws, and their results could have been affected by their potential for selection, performance, and detection biases. Their findings must therefore be interpreted cautiously, as stressed by several authors [12, 39–45]. The TRAAP trial enrolled 4000 women at standard risk for PPH with a planned vaginal delivery of a singleton live fetus at 35 weeks or more of gestation [22]. The primary outcome — blood loss of at least 500 mL — did not differ significantly between women randomized in the tranexamic acid group and those in the placebo group (RR, 0.83; 95% CI, 0.68 to 1.01; *P* = 0.07).

Sixteen RCTs have thus assessed the effect of tranexamic acid in preventing PPH in women who had elective cesareans; they reported a significantly reduced blood loss in those randomized to receive tranexamic acid, with no effect on the cardinal vital signs or on thrombosis [23–38]. Nevertheless, because of their notable methodologic concerns related to blinding, outcome assessment, and attrition bias, their findings must be considered inconclusive. Furthermore, the external validity of the results observed in middle-income countries appears uncertain, and they lacked adequate power to assess severe adverse events [12, 39–45]. The interpretation of their results thus requires particular caution.

Finally, it is important to emphasize that none of these RCTs included cesarean deliveries during labor [12], when moderate and severe blood loss are both significantly more prevalent than before labor [46].

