#### Objectives

The aim of this study is therefore to compare the effect of the administration of a low dose of tranexamic acid (1 g) in the 3 min after a cesarean delivery with placebo, both in addition to prophylactic uterotonics, in a multicenter randomized, double-blind, placebo-controlled trial with two parallel groups.

The specific object ives, similar to but modified from those for the TRAAP trial for vaginal deliveries [22, 39], are as follows:
To assess the effect of tranexamic acid (1 g) on postpartum blood loss after cesarean delivery
Primary outcome
Incidence of PPH defined by a calculated estimated blood loss > 1000 mL [Calculated estimated blood loss = estimated blood volume × (preoperative hematocrit - postoperative hematocrit)/preoperative hematocrit (where estimated blood volume (mL) = weight (Kg) × 85)] or red blood cell (RBC) transfusion before day 2 (D2) postpartum [5–7]. Preoperative hematocrit will be the most recent hematocrit within 1 week before delivery. Postoperative hematocrit will be measured at D2 (see below).Secondary outcomes
Other outcome measures describing postpartum blood loss, including but not limited to calculated blood loss > 500 mL, > 1500 mL and mean total calculated blood loss, mean gravimetrically estimated blood loss by measuring the suction volume and swab weight until discharge from the post-anesthesia care unit (PACU) (i.e., about 2 h after the end of the cesarean) [23] as well as > 500 mL and > 1000 mL; mean gravimetrically estimated blood loss at the end of the cesarean delivery, mean or median number of units of red blood cells transfused, incidence of postpartum iron perfusion, shock, as well as the outcomes previously considered [22, 39]: provider-assessed clinically significant PPH, proportion of women requiring supplementary uterotonic treatment including sulprostone, incidence of postpartum transfusion, incidence of arterial embolization or emergency surgery for PPH, mean peripartum change in hemoglobin and hematocrit as well as hemoglobin drop > 2 g/dL, transfer to intensive care unit (ICU), or death from any cause.To assess the potential adverse effects of tranexamic acid (1 g) after cesarean delivery:
Hemodynamic parameters, adverse gastrointestinal events, renal, hepatic, and coagulation function, and any venous or arterial thrombosis in the 3 months after delivery (39).To assess women’s satisfaction and psychological status at D2 and D60 [39].

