### Sample size

We assumed a 15% incidence of our primary outcome (calculated blood loss > 1000 mL or RBC transfusion before D2) after cesareans in the absence of tranexamic acid, based on the results from a high-quality RCT conducted in the Republic of Ireland with a similar outcome measure (*n* = 2069) [5]. To show a relative reduction of at least 20% in the incidence of postpartum hemorrhage in the tranexamic acid arm — that is, an incidence of 12% or less in this arm, with α = 0.05, 1 − β = 0.80, and a bilateral test, the study will require 2036 women with a cesarean delivery in each group, totaling 4072 participants. A higher number of randomized women must be included given that some will have a scheduled cesarean cancelled, be lost to follow-up, or lack the postpartum blood sample needed to assess the primary outcome (estimated at a maximum of 10%). Accordingly, we plan to include 2262 women in each group, totaling 4524 participants.

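### The Discussion claims adequate power to weigh benefits against risks, but the trial is sized only for PPH incidence and no power for harm is shown

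*Protocol article*

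**What the plan says.** In the Discussion, under Potential and implementation of the findings, the trial "aims to determine with adequate power if the benefits of the routine prophylactic use of tranexamic acid after cesarean delivery significantly outweigh its risks". The Discussion paragraph of the abstract runs on the same lines: "This large, adequately powered, multicenter randomized placebo-controlled trial seeks to determine if the benefits" outweigh the risks.

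The Sample size section covers one outcome. "We assumed a 15% incidence of our primary outcome", with "an incidence of 12% or less in this arm" under tranexamic acid, "with α = 0.05, 1 − β = 0.80, and a bilateral test". From these inputs the article concludes that "the study will require 2036 women with a cesarean delivery in each group, totaling 4072 participants". Allowing for at most 10% losses, 2262 per group are planned.

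Harms appear in three places:
- Objectives lists adverse effects, including "any venous or arterial thrombosis in the 3 months after delivery".
- The clinical adverse-effect list under Secondary outcomes names deep vein thrombosis, pulmonary embolism, myocardial infarction, seizure and dialysis-requiring renal failure, with a closing catch-all for unexpected events.
- Safety consideration adds an independent committee and an interim safety review at half recruitment.

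In the background section on prevention of PPH, the article faults the earlier cesarean trials because "they lacked adequate power to assess severe adverse events".

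**The concern.** Saying that a trial can determine, with adequate power, whether benefit exceeds risk is a statement about the design. It calls for either a sample size that also covers the important harms or a defined benefit-risk measure with its own operating characteristics. The article gives neither. It also treats power for severe adverse events as something a trial should have, since it criticises its predecessors for lacking it.

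This matters because the intervention is prophylactic. On the protocol's own assumption, 85% of untreated women would not have the primary outcome, and the Discussion looks ahead to routine use. When the benefit is spread over many women who would not have bled, a small absolute increase in thrombosis weighs in the balance. A safety comparison described as adequately powered could be read as more reassuring than a handful of events allows.

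**Working it through.** **Step 1: reproduce the plan's own figure.** Inputs from Sample size: p1 = 0.15, p2 = 0.12, two-sided α = 0.05, power 0.80. Pooled-variance formula without continuity correction:

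n = [1.960·√(2·0.135·0.865) + 0.8416·√(0.15·0.85 + 0.12·0.88)]² / 0.03²
= [0.9472 + 0.4063]² / 0.0009 = 1.8320 / 0.0009 ≈ 2035.6, so 2036 per group.

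This matches exactly. Dividing by 0.90 gives 2262.2, against 2262 planned. The calculation is sound, and it concerns PPH only.

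**Step 2: look for a counterpart for harm.** Objectives, Secondary outcomes, Statistical analysis, Sample size and Safety consideration contain no expected rate of thrombosis or other severe event, no detectable difference, no safety margin and no joint benefit-risk measure.

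**Step 3: what 2262 per arm can show for a rare event.** The control risk p is an assumption, shown over a range. The exclusion of women with prior thrombosis makes a low value plausible but does not fix it. Exact power sums the product of the two binomial probabilities over all pairs of event counts for which the two-sided Fisher p-value is at most 0.05. The normal approximation uses the Step 1 formula solved for power. For example, with p = 0.1% against 0.3%:

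z = (0.002 − 1.960·√(2·0.002·0.998/2262)) / √((0.001·0.999 + 0.003·0.997)/2262) = (0.002 − 0.002604)/0.001328 = −0.455, power 32.5%.

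Expected events are 2262·p and 2262·3p.

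| Assumed control risk | Expected events, control / tripled | Fisher, doubling | Fisher, tripling | Normal approx., tripling | Fisher, tripling, 2036 per arm |
|---|---|---|---|---|---|
| 0.05% | 1.1 / 3.4 | 1% | 5% | 18.5% | 4% |
| 0.1% | 2.3 / 6.8 | 6% | 21% | 32.5% | 18% |
| 0.2% | 4.5 / 13.6 | 16% | 49% | 56.8% | 44% |
| 0.3% | 6.8 / 20.4 | 25% | 70% | 74.3% | 64% |
| 0.4% | 9.0 / 27.1 | 34% | 84% | 85.6% | 79% |
| 0.5% | 11.3 / 33.9 | 44% | 92% | 92.2% | 88% |

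**Step 4: thresholds.**
- With 2262 per arm, Fisher power for a tripling is 79% at a control risk of 0.36% and 82% at 0.38%, so 80% is reached at about 0.38%. With 2036 per arm the figure is about 0.42%.
- For a doubling with 2262 per arm, 80% needs a control risk of about 1.1%.
- At 0.1% the relative risk detectable with about 80% power is 6. At 0.2% it is 4 (79%).
- By the normal approximation, 80% power for a tripling from 0.1% needs 7833 per group.
- With no events among 2262 women, the upper 97.5% limit is 1 − 0.025^(1/2262) = 0.163%, which is larger than a control risk of 0.1%.

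**Step 5: objective against outcome list.** Objectives speaks of any venous or arterial thrombosis over 3 months. The clinical adverse-effect list names only deep vein thrombosis, pulmonary embolism and myocardial infarction. Stroke counts as arterial thrombosis in the exclusion criteria, but it is named neither in that list nor among the events in Safety consideration.

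**The case against.** **Sizing on efficacy and estimating safety is normal practice.** This stands. The absence of a power calculation for harm is not itself an error. The fault lies in claiming adequate power for the benefit-risk question.

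**The document as a whole does not hide what was powered.** This largely stands. The Methods paragraph of the abstract ties 80% power to PPH, and the conclusion of the background describes an adequately powered trial of the effect on PPH incidence. In the abstract's Discussion paragraph the phrase can be read as merely describing the trial. The main Discussion is not open to that reading: there adequate power is attached directly to benefits against risks.

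**The power figures rest on a rate the article does not give.** This stands, and it limits the claim. A reader might infer that the trial cannot detect even a tripling of thrombotic risk. The documents do not support that: at a control risk of 0.4%, power for a tripling is 84%.

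**Two further readings go too far.** One is that stroke is not captured. The adverse-effect list has a catch-all, and the 12-week telephone questionnaire described under Data management asks about thromboembolic events, so stroke would probably be recorded. It is simply not a named outcome. The other is that a non-significant safety result would be reported as proof that benefit outweighs risk. The article sets no such rule, and Statistical analysis already plans relative risks and risk differences with 95% confidence intervals.

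**Conclusion.** The point holds as an overstatement in the Discussion, echoed in the abstract. The article states a property, adequate power for the balance of benefit and risk, that its only calculation does not show. That conclusion needs no outside figure.

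Its practical size is conditional. If the control risk of thrombosis lies between 0.1% and 0.3%, power for a tripling is well short to somewhat short of 80%. Above about 0.38% a tripling would be detectable, but a doubling would not be until the control risk is near 1.1%. These figures assume that all 2262 women per arm are analysed and that no multiplicity adjustment applies. Losses lower them, and so would the Benjamini–Hochberg procedure if it is meant to cover the adverse effects listed under Secondary outcomes.

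The mismatch between the thrombosis objective and the listed events is a secondary point about naming and pooling. It does not show that events are missed.

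**What to change.** 1. In the abstract's Discussion paragraph and in Potential and implementation of the findings, confine adequate power to the incidence of PPH, as the conclusion of the background already does.
2. Add there that severe adverse events will be estimated with 95% confidence intervals and that power for rare events is limited. Give detectable relative risks over a stated range of assumed control rates (for example about 6 at 0.1% and about 4 at 0.2%). State that a non-significant difference will not be taken as evidence of safety.
3. As a secondary step, report one pooled outcome of any venous or arterial thrombosis up to 12 weeks, naming stroke, so that the outcome list matches the objective.

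Steps 1 and 2 change wording only and make the stated claim more modest. Step 3 adds one outcome definition and uses data already being collected. None of them affects sample size, visits or the primary analysis.

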## Data Availability

Not applicable.

## Abbreviations

ANSM: National Agency for Drug Safety
aPTT: Active prothrombin time
CEU: Clinical epidemiology unit
CI: Confidence interval
CNIL: *Commission Nationale Informatique et Libertés* (French national data protection agency)
CPP: *Comité de Protection des Personnes* (Committee for protection of persons)
CRT: Clinical research technician
D: Day
DSMC: Data and safety monitoring committee.
eCRF: Electronic Case Report Form
g: Gram
GROG: *Groupe de Recherche en Obstétrique et Gynécologie* (Obstetrics and gynecology research group)
HELLP: Hemolysis elevated liver low platelet
ICU: Intensive care unit
IU: International unit,
Kg: Kilogram
L: Liter
mL: Milliliter
PACU: Post anesthesia care unit
PHRC: *Programme Hospitalier de Recherche Clinique* (hospital clinical research program)
PPH: Postpartum hemorrhage
PPRIGO: *Production pharmaceutique pour la recherche institutionnelle du grand ouest* (pharmaceutical production for Western France institutional research)
PT: Prothrombin time
PVC: Packed cell volume
RBC: Red blood cells
RCT: Randomized controlled trial
RR: Risk ratio
SUSARs: Suspected unexpected serious adverse reactions
TRAAP: Tranexamic acid for preventing postpartum hemorrhage following a vaginal delivery (randomized controlled trial)
TRACOR: Traction of the cord (randomized controlled trial)
TSC: Trial steering committee
WOMAN: World maternal antifibrinolytic (randomized controlled trial)
